### Randomization and Blindness

2.6

Institute of Clinical Pharmacology of Xiyuan Hospital, China Academy of Chinese Medical Sciences took the responsibility of generating the allocation sequence. Consecutive numbers were assigned to each clinical center according to a center-stratified random order generated by SAS9.4 (SAS Institute Inc., Cary, NC), and an interactive voice-response or web-response system will be used to assign each patient a number and group. A researcher who will not participate in this study set up an emergency letter for each blinding number, and emergency letters will be sealed in opaque envelopes. In patients with serious adverse events, an emergency unblinding procedure will be initiated. Meanwhile, the whole process of drug coding and documentation is performed blinded. Participants, clinical investigators, and statisticians will all be blinded until completion of the whole trial.

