**Methods::**

A multi-center, double-blinding, double-dummy, active-controlled, randomized trial will be established. A total of 240 patients in 6 centers with mild active UC (Mayo score is 3–5 points) and TCM syndrome of damp-heat stasis blocking and spleen-qi deficiency will be randomly allocated in the ratio of 1:1 to 2 groups: the experimental group and the control group. The experimental group will receive Hudi enteric-coated capsules (HEC) and enteric-coated mesalazine tablets placebo; the control group will receive enteric-coated mesalazine tablets and HEC placebo. Each group will be treated for 8 weeks. The primary therapeutic outcome: the rate of clinical efficacy and clinical remission at 8 weeks of treatment (last survey point) according to the modified Mayo score. The secondary outcomes: individual symptom score, TCM syndrome score, endoscopic response rate, mucosal healing rate, and quality of life scale score. Outcomes will be assessed at baseline and the end of the trial. Besides, intestinal mucosa, stools and blood biopsies from the mild active UC patients before and after treatment will be collected to reveal the underlying mechanisms.

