### Trial design

2.2

This study is a multi-center, double-blind, double-dummy, randomized, parallel positive controlled trial. We adopted a noninferiority trial design and followed the Standardized Protocol Interventions: Recommendations for Interventional Trials (SPIRIT) 2013 Statement.^[11]^ The experimental group was treated with HEC and enteric-coated mesalazine tablets (EMT) placebo, while HEC placebo and EMT were used in the control group. A total of 240 patients diagnosed with mild active ulcerative colitis (MAUC) and TCM syndrome of damp-heat stasis blocking and spleen-qi deficiency in 6 clinical trial centers are eligible for enrolment. We will implement randomization with a 1:1 allocation ratio in the experimental group (n = 120) or the control group (n = 120), and each patient will undergo an 8-week treatment. The study flowchart is showed in Figure 1.

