### Number of Samples

2.3

Number of Samples was determined based on the calculation of noninferiority trial design. The efficacy rates of EMT ranges from 65% to 71%,^[12,13]^ and the average rate is about 68%. Our previous study found that the efficacy rates of HEC is 83.11% in treating MAUC. The sample size was calculated by the following formula: 

*U*α, *U*β is the corresponding *U* value of α, β. When α equaling to 0.05, β equaling to 0.1, *U*α (0.05) is 1.645, *U*β (0.2) is 0.842. *P*_1_ and *P*_2_ represent the efficacy rates of HEC and EMT. *P* equals to (*P*_1_ + *P*_2_) /2 × 100%. The certainty was set at 80%, considering 20% of sample lose. The sample number was set to 120 for each group, 240 in total, and 40 samples in each center.

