**Table 2 T2:**
[figure not shown]
Modified Mayo score system for assessment of ulcerative colitis activity.

Minor outcomes including individual symptom score, TCM syndrome score, endoscopic response rate, mucosal healing rate, and quality of life scale score.

1.Individual symptom score: referred Guidance Principle of Clinical Study on New Drug of Traditional Chinese Medicine.^[17]^ All symptoms were divided into four levels: none, mild, moderate, and severe. The main symptoms were scored as 0, 2, 4, and 6 points, and the minor symptoms are scored as 0, 1, 2, and 3 points. The tongue and pulse were divided into normal and abnormal grades, 0 and 2 points were recorded in the main symptom, and 0 and 1 points were recorded in the minor symptom.2.TCM syndrome score: The score was graded based on the degree of individual symptom score. All indicators were determined by comparing the values obtained at 2, 4, and 8 weeks with baseline values.Clinical recovery: clinical symptoms disappeared or syndrome score decreased by ≥95% from the baseline;Marked efficacy: the syndrome score decreased by ≥70% and <95% compared with the baseline;Efficacy: the syndrome score was a decrease of at least 30% and less than 70% from the baseline;Invalid: the syndrome score was a decrease of less than 30% from the baseline;Worsen: the syndrome score exceeded the baseline after treatment.TCM syndrome efficacy rate = (Clinical recovery + Marked efficacy + Efficacy) cases /a total number of cases ×100%.Endoscopic response rate: was defined as endoscopic score decreased at least 1 point from the baseline in the modified Mayo score. Endoscopic response rate = endoscopic response cases / total number of the group ×100%.(2)Mucosal healing rate: was defined as absolute subscore for endoscopy of 0 or 1. Mucosal healing rate = Mucosal healing cases / total number of the group ×100%.(3)Quality of life assessment: Patients were evaluated by Inflammatory Bowel Disease Questionnaire,^[18]^ included the 32 most frequent and important items. Inflammatory Bowel Disease Questionnaire was divided into 4 modules: bowel symptoms (10 questions), systemic symptoms (5 questions), emotional function (12 questions), and social function (5 questions). Each question has graded responses from 1 to 7, and thus the total score is ranging from 32 to 224, with higher scores representing a better quality of life.

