### Data analysis

3.7

Data analysis will be performed by professional statisticians and the main researchers using SPSS 22.0. Statistical analysis included the actual number of subjects selected, cases of shedding and rejection, demography and other baseline characteristics, patient compliance, efficacy and safety analysis. We used frequency tables or percentages for categorical variables, and mean ± standard deviation for continuous variables to describe the characteristics of patients in both groups. Categorical data will be analyzed by chi-square test or Fisher exact test to compare the differences between the 2 groups, while quantitative data with normal distribution will be analyzed by *t* test. If the data does not conform to the normal distribution or the uniformity of variance, Wilcoxon rank sum test or Wilcoxon signed test will be used to analyze them to compare the two groups. A two-sided *P-*value <.05 will be set as the significant level.

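### Allocation is stratified by centre, but the named tests use neither centre nor the baseline score as a covariate, and a paired Wilcoxon test is listed for comparing two independent arms

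*Protocol article*

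**What the plan says.** Section 2.6 (Randomization and Blindness) makes centre a stratification factor: "Consecutive numbers were assigned to each clinical center according to a center-stratified random order". Section 2.3 (Number of Samples) fixes the size of the strata: "The sample number was set to 120 for each group, 240 in total, and 40 samples in each center". With 1:1 allocation that is about 20 per arm in each of six centres.

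Outcomes are measured before treatment as well as after it. The abstract states "Outcomes will be assessed at baseline and the end of the trial", and section 3.4, under the TCM syndrome score, adds "All indicators were determined by comparing the values obtained at 2, 4, and 8 weeks with baseline values".

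Section 3.7 (Data analysis) names the tests by type of data:

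- For rates: "Categorical data will be analyzed by chi-square test or Fisher exact test to compare the differences between the 2 groups".
- For scores judged normal: "quantitative data with normal distribution will be analyzed by *t* test".
- For other scores: "Wilcoxon rank sum test or Wilcoxon signed test will be used to analyze them to compare the two groups".

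No stratified test, regression model or covariate is mentioned.

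**The concern.** There are three linked points.

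1. **Centre.** Stratified allocation balances the arms within each centre, so differences between centres largely drop out of the treatment contrast. A test that ignores the strata still counts those differences as noise. Its standard error is then too large, its intervals are too wide and some power is lost. Interval width matters here because section 2.2 describes a noninferiority design.

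2. **Baseline.** The quality-of-life questionnaire (IBDQ), individual symptom and TCM syndrome scores are available at baseline, but the tests named for them have no baseline term. Precision that costs nothing is left unused.

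3. **Signed test.** The Wilcoxon signed test works on within-patient differences. The trial has two parallel arms of different patients, so no pairs exist across arms, and the test cannot do the job that section 3.7 gives it.

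**Working it through.** **Inputs from the article.** Control rate 68%, experimental rate 83.11%, quantiles 1.645 and 0.842, 20% loss, and 120 per group with 40 per centre (section 2.3). Two-sided 5% level (section 3.7).

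**Inputs assumed.** The article gives neither the spread of response rates between centres nor the correlation between baseline and week-8 scores. Both are varied below.

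**Reproducing the plan's sample size.** The formula is not legible in the text at hand, so the usual two-proportion form is tried. The mean rate is P = (0.8311 + 0.68)/2 = 0.75555 and the difference is 0.1511.

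n = 2 × 0.75555 × 0.24445 × (1.645 + 0.842)² / 0.1511² = 100.07

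100.07 × 1.2 = 120.1. The stated 120 per group is recovered, so the rates above are the right ones for judging the effect of stratifying.

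**Effect of ignoring centre.** 40,000 trials were simulated per setting, each with six centres of 20 + 20 patients. Centre effects were spread on the logit scale, with the average rates held at 68% and 83.11% (both 68% for type I error). The unstratified chi-square was compared with the Cochran-Mantel-Haenszel (CMH) test stratified by centre.

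| Assumed logit SD | Control rates by centre | Type I error, unstratified / CMH | Power, unstratified / CMH | Gain |
|---|---|---|---|---|
| 0 | 68% in all | 0.049 / 0.049 | 0.785 / 0.783 | about 0 |
| 0.3 | 58-77% | 0.048 / 0.050 | 0.789 / 0.792 | 0.3 points |
| 0.6 | 47-85% | 0.042 / 0.050 | 0.792 / 0.807 | 1.5 points |
| 1.0 | 35-92% | 0.031 / 0.049 | 0.804 / 0.844 | 4 points |

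The simulation error is about √(0.05 × 0.95/40,000) = 0.001 for type I error and √(0.79 × 0.21/40,000) = 0.002 for power.

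**Hand check of the conservatism.** The unstratified test assumes variance p(1 − p). The actual variance under stratified allocation is smaller by the between-centre variance of the rates.

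- At SD 0.6 the six rates are 0.47, 0.59, 0.66, 0.72, 0.78 and 0.85. Their mean is 0.678, their variance is 0.0155, and p(1 − p) = 0.2182. The ratio is 1 − 0.0155/0.2182 = 0.929. The effective cut-off is 1.96/√0.929 = 2.03, and the two-sided type I error is 0.042.
- At SD 1.0 the rates are 0.35, 0.54, 0.66, 0.76, 0.84 and 0.92, with variance 0.0364. The ratio is 0.833, the cut-off is 2.15, and the type I error is 0.032.

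Both agree with the simulation.

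**Effect of leaving baseline out of the model.** Let r be the correlation of baseline with the week-8 score, with equal variances at the two times. In units of the score variance, a final-value comparison has variance 1, a change-score comparison has 2(1 − r), and ANCOVA has 1 − r².

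| Assumed r | ANCOVA / final value = 1 − r² | ANCOVA / change = (1 + r)/2 |
|---|---|---|
| 0.4 | 0.84 | 0.70 |
| 0.5 | 0.75 | 0.75 |
| 0.6 | 0.64 | 0.80 |

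The reduction is 16-36% against final values and 20-30% against change scores. Section 3.7 does not say which of the two would be tested, but ANCOVA is more precise than either.

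**The signed test.** This needs no arithmetic. Section 2.2 describes a randomised parallel trial, and section 3.7 assigns a paired test to the comparison of its two arms. The two statements do not fit.

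**The case against.** The strongest reply is that section 3.7 is one paragraph of a journal article. Strata and covariates are often left to an analysis plan that is not shown, and a stratified chi-square is still a chi-square. This lowers confidence that no adjustment is planned. It does not remove the point, because the article does name its tests, and as named they carry no stratum or covariate. No further document could make the signed-test sentence correct as it stands.

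Second, the effect of centre is small unless centres differ widely, and the article gives no evidence that they do. Its only reported spread, 65% to 71% for the control drug, is across published sources and not across centres. This stands, and the table shows it.

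Third, baseline is not ignored. Clinical efficacy, endoscopic response and the TCM syndrome grades are all defined relative to baseline in section 3.4. This also stands. What is absent is baseline as a covariate in the between-arm comparison of scores, which concerns secondary outcomes only.

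Fourth, the signed test was probably meant for within-arm change. The rank sum test, which is right for two arms, comes first in the same sentence, and patients are measured before and after treatment. That is the likely intention, but it is not what the sentence says.

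A reader might infer more: that ignoring the strata inflates false positives, biases the result or leaves the trial badly underpowered. The documents do not support this. Type I error falls below 5%, and at the protocol's own rates the unstratified test keeps about 79-80% power. Nor does any passage describe pairing patients across arms.

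**Conclusion.** The point holds as one definite misstatement plus an avoidable loss of precision. The Wilcoxon signed test is wrongly listed for comparing independent arms; this rests on no assumption. The unstratified tests are valid and err on the conservative side. Stratifying is worth 0 to 4 points of power over the assumed centre spreads, and at most about 1.5 points unless centres differ very widely. The baseline gain for scores is larger, but it depends on correlations that the article does not give.

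The power figures are for the two-sided 5% test of difference named in section 3.7, at full enrolment without loss and with equal centres. They do not describe power against a noninferiority margin, since the article states none; that is a separate matter which this change does not settle.

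**What to change.** In section 3.7:

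- Analyse the binary endpoints (clinical efficacy, clinical remission, endoscopic response, mucosal healing, TCM syndrome efficacy) by a centre-stratified Mantel-Haenszel risk difference with its confidence interval. Unlike a chi-square or Fisher P value, this also gives an interval for the treatment effect.
- Analyse the IBDQ, individual symptom and TCM syndrome scores by ANCOVA on the week-8 value, with treatment, centre and baseline score as terms.
- Keep the Wilcoxon rank sum test for between-arm comparison, and restrict the Wilcoxon signed test to within-arm change.

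The cost is a change of wording, made before unblinding. Centre and baseline scores are already collected, and sample size, visits and procedures do not change. If centres turn out alike, stratifying costs almost nothing (power 0.783 against 0.785).

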1.The participant is not willing to continue the clinical trial.2.No medication or any follow-up records;3.Important deviations occur in the process of the clinical trial, such as poor compliance.4.Occurrence of allergic reactions or serious adverse events during the trial.5.Not alleviated or the symptoms are aggravated.

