### Safety assessment

3.5

Adverse events (AEs) will be documented and assessed by the local principal investigators during this trial, including clinical signs, symptoms, and laboratory tests. All patients will undergo the following laboratory texts between the start and end of the trial. The safety assessment indices included blood pressure, respiration rate, heart rate, body temperature, and physical examination in addition to blood routine examination, urine routine test, stool routine examination and occult blood, liver function tests (AST, ALT, TBIL, DBIL, γ-GT, ALP), kidney function tests (Scr, BUN) and electrocardiogram. Any AEs will be requested to record in electronic CRFs (eCRFs) regardless of their relationship to the intervention. Severe AEs will be stopped immediately and reported to the local drug administration authorities within 24 hours including a detailed description of the time, severity, possible relationship with the drug, and the treatment measurement will be recorded.

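### Unblinding is triggered by any serious adverse event without a stated condition, and nothing requires the relatedness judgement to be recorded first

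*Protocol article*

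**What the plan says.** Four statements in the protocol article bear on this.

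- **Trigger (section 2.6, Randomization and Blindness):** "In patients with serious adverse events, an emergency unblinding procedure will be initiated".
- **Means (same paragraph):** a researcher outside the study "set up an emergency letter for each blinding number, and emergency letters will be sealed in opaque envelopes". One patient can therefore be unblinded without exposing the rest of the code.
- **Blinding promise (same paragraph, two sentences after the trigger):** "Participants, clinical investigators, and statisticians will all be blinded until completion of the whole trial".
- **Safety reporting (section 3.5, Safety assessment):** "Adverse events (AEs) will be documented and assessed by the local principal investigators during this trial". The report to the authorities is due within 24 hours, "including a detailed description of the time, severity, possible relationship with the drug, and the treatment measurement will be recorded".

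In addition, the termination and withdrawal criteria in section 2.5 (Eligibility criteria) include: "Occurrence of allergic reactions or serious adverse events during the trial".

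**The concern.** The trigger in section 2.6 is the event itself. As worded, an event plainly unrelated to treatment, or one that would be managed identically in either arm, starts the same procedure as one where the allocation matters. The blinding sentence does not acknowledge this exception, so a site cannot tell from the text when the blind should be kept after a serious event.

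What is at stake is the safety comparison. The Introduction makes safety part of the primary aim, and the comparison is between a herbal product and a drug with a known adverse-event profile. If the person judging relatedness knows the arm, prior beliefs about either product can shape the judgement, in either direction. Because the trigger covers all serious events, the exposure could reach every serious-event causality judgement.

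**Working it through.** The main check sets the provisions side by side. The plan gives no figure on this point to reproduce.

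**1. Is the trigger conditional?** Section 2.6 says the procedure will be initiated, not that it may be, and adds no test of need. It does not say who decides, who opens the letter or who is told the result. The event alone is enough to start the procedure.

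**2. Is the blinding sentence consistent with the trigger?** It covers participants, investigators and statisticians to the end of the trial, with no exception. For a patient whose letter is opened, the two sentences cannot both be literally true. The natural reconciliation is that an individual code break is an exception to general blinding. The text neither says so nor sets the limits of that exception.

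**3. Can relatedness be judged after unblinding?**

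| Question | Section 2.6 | Section 3.5 |
|---|---|---|
| What starts it? | A serious adverse event | An adverse event, with 24-hour reporting for those called severe |
| Who acts? | Not stated | Local principal investigators assess |
| When? | Not stated | Report within 24 hours |
| Order relative to the other? | Not stated | Not stated |

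Both processes can start from the same event and overlap within a day. Neither section requires relatedness to be recorded first, or by someone who stays blinded. A judgement made with the arm known is therefore permitted, though not prescribed. One caveat is that section 3.5 calls the events with 24-hour reporting severe, while section 2.6 says serious. I read these as the same events, which is an assumption.

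**4. Does it reach the week-8 outcome?** A serious event meets a termination and withdrawal criterion in section 2.5, so later scoring of an unblinded patient is largely pre-empted.

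**5. How many patients?** Section 2.3 (Number of Samples) gives the total: "The sample number was set to 120 for each group, 240 in total, and 40 samples in each center". The article gives no serious-event rate, so I assume 1% to 5%. Expected number = rate × 240:

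- 1%: 0.01 × 240 = 2.4
- 5%: 0.05 × 240 = 12

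That is about 2 to 12 patients entering the procedure.

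**The case against.** The strongest reply is that this is ordinary emergency unblinding, condensed for a journal. The letters, the trigger and the blinding promise share one paragraph, and each letter exposes one patient only. Starting a procedure is not the same as opening a letter. The full protocol may contain a check of need and name the person who learns the allocation, and an article may leave such steps out.

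Part of this stands. A reader might infer that section 2.6 flatly contradicts itself. The documents do not support that, because an individual code break reads naturally as an exception to general blinding. A reader might also infer that investigators will judge relatedness knowing the arm. No section says that the assessor receives the code or judges after it is broken.

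Two further inferences also go too far. One is that the code would be broken preferentially in treatment failures, for example patients hospitalised with a flare, and so bias efficacy. The article does not define serious events or class such a flare as one, it lists aggravated symptoms as a separate withdrawal criterion, and withdrawal limits later scoring. The other is that many patients would be affected. The population has mild disease, is treated for 8 weeks and excludes major comorbidity and serious complications, so the upper end of the assumed range may be high.

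What the reply does not remove is the printed rule. Its wording makes every serious event a trigger. That is a rule stated too broadly, not a detail left for another document.

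**Conclusion.** The point holds in a limited form. Section 2.6 ties the start of unblinding to every serious adverse event without a condition, and its blinding sentence does not recognise the exception. Together with section 3.5, this leaves serious-event causality open to judgement with the arm known.

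The consequence is confined to the safety assessment of patients with a serious event. Their number cannot be derived from the article, and the range of about 2 to 12 of 240 rests entirely on the assumed 1% to 5% rate. The effect on the week-8 primary outcome is probably small. The conclusion also assumes that the 24-hour reporting rule covers the same serious events, and that the full protocol adds no ordering or need check that the article omits.

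**What to change.** - **Section 2.6:** reconcile the two sentences, so that a serious event does not by itself open the code and the blinding sentence names emergency code breaks as its exception. The clinical condition for a break is for the sponsor to set.
- **Section 3.5:** require the relatedness judgement to be recorded before the letter is opened, where this does not delay care. Use one term for the events subject to 24-hour reporting and to section 2.6.
- **Access:** state who may learn the allocation after a break, and keep that group as small as the situation allows.
- **Reporting:** list every code break with its date and reason.

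The cost is a change of wording plus a small documentation step at the time of a serious event. The individual letters already exist. A separate blinded outcome assessor at each of the six centers is not part of this request. Section 2.7 (Research personnel) has the same physicians recruit and evaluate, so that could need extra staff, and the probably small effect on the primary outcome does not call for it.
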